### Data analysis

The primary analysis will be conducted using a linear mixed-effects model, with fixed effects for group (acupuncture, running, Tai Chi), time (baseline, week 2, week 4), and their interaction, and a random intercept for participants to account for within-subject correlation due to repeated measurements. Baseline GPS score, age, sex, and baseline ERP indices will be included as covariates to control for inter-individual variability in procrastination-related traits.

This mixed-effects modeling framework constitutes the primary analytic strategy and will be implemented under the intention-to-treat (ITT) principle, allowing inclusion of all available observations without imputing missing values, under a missing-at-random assumption.

Prior to model fitting, distributional characteristics of continuous variables will be assessed using the Shapiro–Wilk test. Descriptive comparisons of baseline demographic and clinical characteristics will be performed using analysis of variance (ANOVA) or the Kruskal–Wallis test for continuous variables, and chi-square or Fisher's exact tests for categorical variables, as appropriate, to ensure baseline comparability between groups.

Secondary and exploratory analyses may include pairwise comparisons or non-parametric tests (e.g., Mann–Whitney *U*-test or Wilcoxon signed-rank test) where appropriate for specific outcomes or sensitivity checks. For outcomes with repeated measurements that meet parametric assumptions, repeated-measures ANOVA may be used as a supplementary analysis; otherwise, non-parametric alternatives such as the Friedman test will be applied.

Sensitivity analyses will be conducted to evaluate the robustness of the primary findings, including per-protocol analyses restricted to participants with adherence ≥80% and models incorporating adherence (number of completed sessions) as a continuous covariate.

For secondary outcomes and exploratory ERP analyses involving multiple indices or task conditions, false discovery rate (FDR) correction will be applied within pre-defined families of related comparisons. Statistical significance will be defined as a two-sided *P*-value < 0.05. All analyses will be performed using PASS 18.0, with statistical consultation provided by an institutional biostatistician.

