#### Inclusion criteria

Preset study inclusion criteria are as follows:

Full-time university student;GPS score ≥ 70 points;No psychotropic drug intake or related acupuncture treatment within the past 30 days;Providing informed consent.

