## Outcomes

### Primary outcome

General Procrastination Scale (GPS) will be used as the primary outcome measure. The GPS is one of the most widely used and validated trait procrastination scales and has demonstrated good applicability for Chinese college students. It consists of 20 items scored on a 5-point Likert scale from “strongly disagree” (1 point) to “strongly agree” (5 points), and covers multiple domains including academic activities and activities of daily living (52). Note that higher scores on certain items are indicative of greater procrastination while higher scores on others are indicative of lower procrastination tendency, so some item scores are reversed before summation. After appropriate reversal, a higher total score is indicative of greater procrastination tendency, with a score between 20 and 49 points indicating low, 50–69 moderate, and 70–100 high procrastination. Xue and colleagues reported a Cronbach's α coefficient of 0.807 and a test–retest correlation coefficient of 0.756 after 4 weeks, indicating good internal consistency and reliability (53). Exploratory and confirmatory factor analysis revealed a two-factor structure consisting of active avoidance and lack of planning, and the model fitting effect was good (CFI=0.914, TLI=0.901, RMSEA=0.069, SRMR = 0.072). The GPS was also positively correlated with total scores on the Irrational Procrastination Scale and the Academic Burnout Scale (r = 0.753, 0.677, all *P* < 0.001), supporting good reliability and validity (54).

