#### Sample size

Sample size estimation was informed by pilot data and by consideration of realistic and conservative effect size assumptions appropriate for behavioral intervention studies. In a pilot study, post-intervention General Procrastination Scale (GPS) scores were 32.5 ± 6.8 in the acupuncture group, 38.2 ± 7.2 in the running group, and 41.6 ± 6.5 in the Tai Chi group after 8 weeks of intervention. Importantly, similar between-group trends were already observable at 4 weeks, supporting the feasibility of a 4-week intervention in the present trial.

However, given the exploratory nature of the current study and the risk of overestimating effects based on pilot data, sample size calculation for the main trial was performed assuming a conservative medium-to-large effect size. Using G^*^Power 3.1, a one-way analysis of variance (ANOVA) design with three intervention groups was specified, with a two-sided significance level of α = 0.05 and statistical power (1–β) = 0.90. An effect size of Cohen's *f* = 0.40 was selected, consistent with effect sizes commonly reported in behavioral and non-pharmacological intervention studies targeting self-regulation and cognitive control outcomes.

Under these assumptions, the required sample size was estimated to be 27 participants per group. Allowing for an anticipated dropout rate of approximately 10%, the final target sample size was set at 30 participants per intervention group, resulting in a total of 90 participants with high procrastination tendencies. In addition, 30 healthy control participants without procrastination will be recruited to provide normative behavioral and electrophysiological reference values.

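### The primary mixed model uses baseline GPS as both response and covariate with only a random intercept: the covariate is redundant for group-by-time contrasts, and an adjusted week-4 difference gets a distorted slope and too small a standard error

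*Protocol article*

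**What the plan says.** The primary outcome is GPS: "General Procrastination Scale (GPS) will be used as the primary outcome measure" (Primary outcome). The Data analysis section gives the primary model fixed effects for group, "time (baseline, week 2, week 4), and their interaction, and a random intercept for participants". It continues: "Baseline GPS score, age, sex, and baseline ERP indices will be included as covariates". It also states: "This mixed-effects modeling framework constitutes the primary analytic strategy".

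So the baseline GPS value is one of three response times and also a predictor of all three. The random intercept is the only within-person covariance named. The section does not say whether the treatment effect is read from the group-by-time terms or from an adjusted group difference at week 4. Pairwise comparisons appear only among the possible secondary and exploratory analyses.

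Entry requires "GPS score ≥ 70 points" (Inclusion criteria), so participants are selected on the same scale that serves as the baseline response.

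**The concern.** A covariate that equals the first response creates two problems.

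- It is constant within a participant, so it cannot inform a within-person change. Any contrast of week 4 minus baseline is left unadjusted, although the covariates are there to control for differences between individuals.
- Once baseline GPS is a predictor, the baseline rows are almost perfectly predicted by themselves. Their residual variance is then far below that at weeks 2 and 4. A random intercept assumes one common variance and one common correlation, so it averages the near-zero baseline residual with the later ones.

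At stake are the precision of the primary comparison and, for one plausible way of reporting it, the type I error. The model is fully stated here, so a later analysis plan could cure this only by departing from the text.

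**Working it through.** **Inputs.**
- n = 30 per group (Sample size).
- 4-week test-retest correlation ρ = 0.756 (Primary outcome).
- SD from the pilot values 6.8, 7.2 and 6.5 after 8 weeks (Sample size): √[(6.8² + 7.2² + 6.5²)/3] = 6.84, so σ² = 46.79.
- The article gives neither a baseline SD in the selected population nor a 2-week GPS correlation. Values for these are assumptions.

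**The plan's own figure.** In the Sample size section, "one-way analysis of variance (ANOVA) design with three intervention groups was specified", with f = 0.40 and "a two-sided significance level of α = 0.05 and statistical power (1–β) = 0.90"; "the required sample size was estimated to be 27 participants per group". The noncentral F distribution gives power 0.895 at 27 per group and 0.907 at 28. The figure therefore reproduces to rounding, and 27/0.9 = 30. The point below does not alter N.

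**Reading 1: group-by-time contrast (week 4 minus baseline), two groups.** With complete data the baseline covariate cancels. In every simulated trial the estimate was the same with and without it. A mixed-model fit to one simulated data set gave −2.727 (SE 1.115) both ways. With equal variances and correlations:
- Change-score variance: (2/n) × 2σ²(1 − ρ) = (2/30) × 2 × 46.79 × 0.244 = 1.522, so SE = 1.23.
- Week-4 ANCOVA variance: (2/n) × σ²(1 − ρ²) = (2/30) × 46.79 × 0.4285 = 1.336, so SE = 1.16.
- Ratio: 2/(1 + ρ) = 2/1.756 = 1.14. It would be 1.33 at ρ = 0.5 and 1.54 at ρ = 0.3.

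**Reading 2: adjusted group difference at week 4.** The covariate's slope is fitted to the participant's mean over three visits, one of which is baseline itself: b = (1 + 2ρ)/3 = 2.512/3 = 0.84, where the week-4 regression slope is 0.756. The residual variances after this adjustment are:
- Baseline rows: (1 − b)²σ² = 0.0265 × 46.79 = 1.24.
- Week-2 and week-4 rows: (1 + b² − 2bρ)σ² = 0.4351 × 46.79 = 20.36.
- What the random-intercept model assumes at every visit: (1.24 + 20.36 + 20.36)/3 = 13.98 (from unrounded terms).

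The model SE is √(13.98 × 2/30) = 0.97. The true SE is √(20.36 × 2/30) = 1.16, or 1.18 in simulation, where b is estimated. With the closed-form values the SE ratio is about 0.83. A nominal 1.96 cut-off then acts as 1.96 × 0.83 = 1.62, a two-sided error of about 10%. The simulation gave 10.6%.

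**Simulation** (8,000 trials per row, 30 per group, complete data, no treatment effect; age, sex and ERP covariates omitted). Correlations are listed as weeks 0–2, 0–4, 2–4. SD is 6.84 unless given. Each cell shows model SE / true SE, then type I error.

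| Assumed structure | Group-by-time, week 4 | Adjusted week-4 difference |
|---|---|---|
| all 0.756 | 1.23 / 1.24, 5.1% | 0.97 / 1.18, 10.6% |
| all 0.5 | 1.77 / 1.78, 5.3% | 1.32 / 1.57, 9.6% |
| all 0.3 | 2.08 / 2.12, 5.7% | 1.50 / 1.77, 9.5% |
| 0.85, 0.756, 0.85 | 1.06 / 1.23, 8.8% | 0.88 / 1.17, 14.1% |
| 0.7, 0.5, 0.7 | 1.51 / 1.76, 9.6% | 1.20 / 1.57, 13.6% |
| baseline SD 5; 0.6, 0.5, 0.7 | 1.46 / 1.58, 6.5% | 1.22 / 1.54, 12.1% |
| baseline SD 4; 0.5, 0.4, 0.7 | 1.52 / 1.64, 7.0% | 1.30 / 1.62, 11.8% |
| SD 4, 6, 7.5; 0.5, 0.35, 0.7 | 1.55 / 1.84, 9.8% | 1.31 / 1.82, 16.0% |

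The mean ANCOVA standard error stayed within about 2% of the true one in every row.

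**The case against.** The best defence is that the primary model is specified through group, time and their interaction, and the interaction survives well. The difference in change is unbiased in a randomised trial. Under equal variances and correlations its standard error is right. The omnibus four-degree-of-freedom interaction test held 4.9 to 5.5% for assumed 2-week correlations from 0.756 to 0.82, and 5.5 to 5.9% at 0.87. All of this stands. It also limits what may be inferred.

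- *That the week-4 standard error is wrong whatever is reported.* Not supported. For the group-by-time contrast this depends on unequal variances or correlations, and the article reports no figures that establish either.
- *That the entry threshold alone proves inflation.* Not supported. With GPS cut at 70 (assumed population mean 55 to 60, SD 10 to 12) and a correlation of 0.756 throughout, the pairwise error was 4.4 to 4.9%. It was 5.2 to 5.4% at a 2-week correlation of 0.78, 6.0 to 6.4% at 0.807, and reached 9 to 10% only at 0.87. That last value is hard to reconcile with the reported Cronbach's α of 0.807, although α is not a strict ceiling.
- *That baseline adjustment does nothing at all.* This is exact only for group-by-time contrasts in complete data. The article expects about 10% dropout, and no missing visits were simulated.
- *That the treatment effect is diluted by averaging over a pre-treatment visit.* This would apply only if the group main effect were the treatment test, which the article nowhere says.

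A random intercept is also a common choice, and degrees-of-freedom methods may be left to an analysis plan. What remains is that the double use of baseline is a stated rule, and that the article names no contrast to keep a reader away from the reading under which the standard error fails.

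**Conclusion.** The point holds in this form: baseline GPS is used twice in the primary model, and the consequence depends on a contrast that the article does not name.

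- **Group-by-time contrast.** The result is an unadjusted change-score comparison. The cost is efficiency, a variance about 1.14 times that of ANCOVA at ρ = 0.756 with equal variances. Type I error for a pairwise week-4 contrast is near 5% under equal variances and correlations. It is about 6 to 10% in the five unequal structures tabulated, whose correlations or SDs are assumed. The omnibus interaction test stays near 5 to 6%.
- **Adjusted week-4 difference.** The slope is 0.84 instead of 0.756 and the standard error is too small in every case tried (0.97 against 1.18 under equal correlations). Type I error is about 10 to 16%. This failure needs no assumption that correlations decay.

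The absolute standard errors rest on the pilot SD of 6.84, which comes from 8 weeks rather than 4, and on complete data.

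**What to change.** Use baseline GPS once, in one of two ways:

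1. Take GPS at weeks 2 and 4 as the response, with group, time, group-by-time, baseline GPS and baseline-by-time as fixed effects; or
2. Keep baseline, week 2 and week 4 as response levels with a common baseline mean across the three groups, and remove baseline GPS from the covariates.

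In either case replace the random intercept with an unstructured within-person covariance, and name the week-4 group difference as the primary contrast.

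The price is a few more covariance parameters: three for two visits or six for three, against two for a random intercept with residual variance. The change is one of wording in the Data analysis section. It needs no new data, and the planned 30 per group stands.

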#### Exclusion criteria

The following exclusion criteria will be applied during enrolment:

Organic mental disorders, diseases related to surgical history, and current use of psychoactive substances;Family history of other mental illnesses such as dementia, schizophrenia, mania, and addiction;Impaired consciousness or agitation, or otherwise unable to cooperate with task completion or EEG collection;Skin lesions or skin diseases.

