##### Dropped cases will be handled as follows:

After drop out, the attending doctor will try to contact the subject by phone or letter to obtain the reason(s) and schedule a final visit if possible to complete the assessable items.For cases that quit the trial due to adverse reactions or ineffective treatment, the attending doctor will take appropriate measures in accordance with current treatment guidelines.The “Summary of Treatment Completion” and “Clinical Trial Completion” in the CRF will be filled in.All excluded and dropped cases will be included in the intention-to-treat analysis after the trial ends.

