### Measurement of event-related potentials by EEG

A total of 120 participants will be recruited, including 90 with high levels of procrastination to be allocated randomly and equally to acupuncture, running, and Tai Chi groups, and a healthy control group (n = 30). All members of the research team received systematic training in EEG data acquisition and analysis, and participated in the full workflow of the pilot study, including data collection and pre-processing. EEG data will be recorded using a 32-channel actiCHamp Plus system (Brain Products, Germany). Electrodes will be placed according to the international 10–20 system, with bilateral mastoids serving as reference electrode points. Electrode impedances will be maintained below 5 kΩ, and signals will be sampled at 500 Hz. Online filtering will include a high-pass filter (0.1–0.5 Hz), a low-pass filter (30–50 Hz), and a 50 Hz notch filter to eliminate line noise. Data analyses will focus on midline frontal (Fz), central (Cz), parietal (Pz), and lateral frontal (F3, F4) electrodes. Pre-processing procedures, including filtering, artifact rejection, and independent component analysis (ICA), will be performed using MATLAB R2020b and EEGLAB v2019.0.

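### Baseline ERP covariates in the primary GPS model conflict with the intention-to-treat, no-imputation statement: anyone without a usable baseline ERP would leave the analysis

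*Protocol article*

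**What the plan says.** The Data analysis section makes a linear mixed-effects model the primary analysis of GPS, with group, time (baseline, week 2, week 4), their interaction and a random intercept per participant. On covariates it says: "Baseline GPS score, age, sex, and baseline ERP indices will be included as covariates".

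The next paragraph says that this same model "will be implemented under the intention-to-treat (ITT) principle", "allowing inclusion of all available observations without imputing missing values, under a missing-at-random assumption".

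The rules for dropped cases point the same way: "All excluded and dropped cases will be included in the intention-to-treat analysis after the trial ends".

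Two other places bear on whether a baseline ERP can be absent. The section on measuring ERPs says: "Pre-processing procedures, including filtering, artifact rejection, and independent component analysis (ICA), will be performed". The exclusion criteria remove, at enrolment, people who are "otherwise unable to cooperate with task completion or EEG collection".

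The Sample size section allows about 10% for dropout and makes no separate allowance for unusable EEG.

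**The concern.** Likelihood-based mixed models keep a participant who misses a visit, because the remaining outcome rows still contribute. That is what the missing-at-random statement relies on. It does not extend to covariates: a row with an empty covariate cannot enter the likelihood unless the value is filled in or modelled. A baseline ERP index has the same value at every visit, so if it is missing, all of that participant's GPS rows go. If several indices are in the model, the participant needs every one of them.

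A participant could therefore complete all sessions and all GPS assessments and still be left out of the primary analysis because of one poor EEG recording. The analysed set would be defined by EEG quality, although the text promises intention-to-treat. The primary question is about a questionnaire score, and nothing about it requires EEG.

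**Working it through.** **1. The plan's own figure.** Inputs from Sample size: one-way ANOVA, 3 groups, Cohen's f = 0.40, two-sided α = 0.05, power 0.90, 27 per group, about 10% dropout, 30 per group.

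Power = P(F′ > F crit), where F′ is noncentral F with 2 and N − 3 degrees of freedom and noncentrality f²N.

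- At 27 per group: N = 81, noncentrality 0.16 × 81 = 12.96, power 0.895.
- Dropout: 27 / (1 − 0.10) = 30, as stated.
- At 30 per group: N = 90, power 0.926.

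The stated 27 reproduces to within half a percentage point of power. Exactly 0.90 is first passed at 28 per group (0.907). That difference is minor and is not part of this point. The fair comparator below is therefore 0.895, not 0.90.

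**2. What a missing baseline covariate does.** 90 participants × 3 visits = 270 GPS rows. In a simulated data set with a random-intercept model, 9 of 90 participants were given no baseline ERP value and no imputation was done. The fitted data fell from 270 to 243 rows and from 90 to 81 participants. That is 9 × 3 = 27 complete GPS rows removed for an EEG reason.

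**3. Size under an assumed rate.** Let m be the share of randomised participants without a usable baseline ERP. The article does not give m; every value below is an assumption.

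- Participants lost = 90 × m.
- Per arm before dropout = 30 × (1 − m).
- Per arm after 10% dropout = 30 × (1 − m) × 0.9, taking the two losses as independent.

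| m (assumed) | Lost of 90 | Per arm before dropout | Power | Per arm after dropout | Power |
|---|---|---|---|---|---|
| 0% | 0 | 30 | 0.926 | 27 | 0.895 |
| 5% | 4.5 | 28.5 | 0.912 | 25.7 | 0.878 |
| 10% | 9 | 27 | 0.895 | 24.3 | 0.858 |
| 15% | 13.5 | 25.5 | 0.876 | 22.9 | 0.836 |
| 20% | 18 | 24 | 0.853 | 21.6 | 0.810 |

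In whole participants per arm, power is 0.883 at 26, 0.869 at 25, 0.854 at 24 and 0.837 at 23. At m = 10% the whole dropout allowance is used up before anyone drops out.

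**4. Limits of the proxy.** The figures use the protocol's ANOVA, not the planned mixed model. The right-hand columns remove dropouts completely, whereas the mixed model would keep their available visits, so they overstate the effect of dropout. The pre-dropout columns show the picture without that. The EEG-related part after dropout is 0.895 − 0.878 = 0.017 at 5% and 0.895 − 0.836 = 0.059 at 15%, or roughly 2 to 6 percentage points.

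**The case against.** **There may be no loss.** Nothing in the article shows that any baseline EEG will be unusable. People who cannot cooperate with EEG are excluded at entry, and artifact rejection is listed as pre-processing, with no rule that discards whole participants. This stands, and it makes the point conditional. It does not remove it: the entry screen cannot catch a recording found unusable after processing, and the promise to analyse everyone should not depend on perfect EEG.

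**This is detail for an analysis plan.** Which indices enter, and how a missing baseline covariate is handled, may well be settled in a document not shown, and neither is counted here as missing. The no-imputation clause is also usual wording for repeated outcomes. But the article itself puts the ERP covariates, the intention-to-treat claim and the absence of imputation on one model without limiting that clause to outcomes, and those stated items do not fit together.

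**The rule for dropped cases concerns withdrawals and mistaken admissions, not EEG quality.** True. It is supporting evidence of the intention to keep everyone, no more.

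**Stronger readings that a reader might infer, and why they fail:**

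- *That the model carries up to 160 ERP covariates.* The count comes from crossing 2 components × 2 measures × 5 electrodes × 8 conditions. The article says "Data analyses will focus on midline frontal (Fz), central (Cz), parietal (Pz), and lateral frontal (F3, F4) electrodes", but that describes the EEG analysis and does not make every cell a covariate. The Expected results section names far fewer indices.
- *That the adjustment can be chosen after seeing results.* This rests on an index list that may be fixed elsewhere.
- *That ERP covariates are useless because they do not vary over time.* The same holds for age and sex. In a simulated complete data set, the standard error of the group-by-time contrast was 1.451 with no covariate, with an ERP-like one and with age. This is no reason to single out ERP.
- *That the comparison between arms would be biased.* The measure is taken at baseline and EEG recorders are to be blinded to allocation, so loss that differs by arm is not evident.

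**Conclusion.** The concern holds as a conditional conflict within the stated text. With baseline ERP indices as covariates and no imputation, the primary GPS model becomes an EEG-complete-case analysis as soon as one randomised participant lacks a usable baseline ERP, which contradicts the intention-to-treat statements.

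The size cannot be derived from the article. At an assumed 5–15% unusable, about 5 to 14 of 90 participants would go, and proxy power after 10% dropout would be about 0.84–0.88 against 0.895. If all recordings are usable, nobody is lost. The power cost is modest; what matters more is that the analysed set would not be the one promised for the primary outcome. The documents do not support a claim that loss is certain or that the treatment comparison is biased.

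**What to change.** In Data analysis, delete baseline ERP indices from the covariates of the primary GPS model and leave baseline GPS, age and sex. Add one sentence: a sensitivity or exploratory model will include baseline ERP, will be labelled as restricted to participants with usable baseline EEG, and will report the number analysed per arm.

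The cost is one deleted phrase and one added line, with no new data. The small downside is that if baseline ERP predicts dropout, the primary model loses whatever support it gave to the missing-at-random assumption; the sensitivity model would still show that.

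If the sponsor prefers to keep ERP in the primary model, the alternative is to state a rule for missing baseline covariates and to limit the no-imputation sentence to outcomes. That also resolves the conflict but needs more text and one more assumption.

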## Methods/design

### Study setting

This parallel randomized controlled clinical trial will be conducted at Third Affiliated Hospital of Henan University of Chinese Medicine, Henan Province, China, according to the principles outlined in Consolidated Standards of Reporting Trials (CONSORT), Standards for Reporting Interventions in Acupuncture Clinical Trials (STRICTA), and Standard Protocol Items: recommendations for Interventional Trials (SPIRIT) guidelines (Figure 1). Ninety full-time college students will be randomly and equally assigned to acupuncture, running, and Tai Chi groups. The allocated intervention will be conducted for 30 min, 3 times per week on alternating weekdays for a total of 4 weeks (w). The General Procrastination Scale (GPS) will be used as the primary outcome measure, with the Procrastination Assessment Scale for Students (PASS) and Physical Activity Rating Scale 3 (PARS-3) used as secondary outcome measures. Outcome measures will be conducted at baseline (0 w) and after 2 and 4 weeks of intervention. In addition, P300 and N200 will be measured by scalp EEG during the Go/No-go Emotion Detection task and Task Initiation Delay Paradigm (TIDP) to observe the effects of these interventions on cognitive control and error detection abilities.

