### Secondary outcomes

The Procrastination Assessment Scale for Students (PASS) was developed by Solomon and Rothblum in 1984 to measure students' academic procrastination behavior, including for coursework, test preparation, and essay writing (55). In the proposed study, the first part of the scale, revised by Hou and Gai (56), will be used as a secondary outcome measure. This section consists of 18 items covering 6 tasks: “writing term papers”, “reviewing exam preparations”, “academic assignments assigned by teachers”, “academic administration tasks”, “attendance assignments”, and “general school activities”. All items are scored on a 5-point Likert scale, and the scores of the first two items related to each of the six tasks are added together to calculate 6 task subscores from 2 to 10. The total score ranges from 12–60 points, with a higher score indicating a higher degree of academic procrastination. A total score >36 indicates problematic academic delay, while a subscore > 6 indicates procrastination on a specific task. In the proposed study, a score of 24 will be defined as severe procrastination. A previous study reported a Cronbach's α coefficient of 0.82 and test–retest coefficient of 0.78 after 2 weeks, indicating good internal consistency and reliability. Exploratory and confirmatory factor analysis demonstrated a three-factor structure, and model fitting was good (CFI = 0.921, TLI = 0.912, RMSEA = 0.071, SRMR = 0.068). Further, Yip and colleagues reported that the PASS score was significantly correlated with both the GPS score and academic performance (*r* = 0.65, 0.45, all *P*% 3C0.001), supporting good construct validity (55).

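### For PASS and the ERP indices the plan permits between-arm tests that do not condition on the outcome's own baseline, although that baseline is collected; this gives up some precision at no saving

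*Protocol article*

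**What the plan says.** Under Study setting the protocol article lists the outcomes, "with the Procrastination Assessment Scale for Students (PASS) and Physical Activity Rating Scale 3 (PARS-3) used as secondary outcome measures", and gives the schedule: "Outcome measures will be conducted at baseline (0 w) and after 2 and 4 weeks of intervention". A week-0 PASS score will therefore exist for each participant assessed. Baseline ERP indices will exist too, because the primary model uses them.

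The Data analysis section describes one covariate-adjusted model, introduced as the primary analysis. It is a linear mixed model with group, "time (baseline, week 2, week 4), and their interaction, and a random intercept for participants". Its covariates are listed: "Baseline GPS score, age, sex, and baseline ERP indices will be included as covariates". Baseline PASS is not among them, and no corresponding model is written for PASS or for an ERP index as the response.

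For the remaining outcomes the section says "Secondary and exploratory analyses may include pairwise comparisons or non-parametric tests", giving Mann-Whitney and Wilcoxon signed-rank as examples, to be used where suitable for particular outcomes or as sensitivity checks. A parametric supplement is offered next: "For outcomes with repeated measurements that meet parametric assumptions, repeated-measures ANOVA may be used as a supplementary analysis". If those assumptions fail, the section falls back on rank methods: "otherwise, non-parametric alternatives such as the Friedman test will be applied". FDR correction is planned within families of secondary and ERP comparisons.

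**The concern.** None of the tests named for secondary and exploratory outcomes uses the outcome's own baseline as a covariate. Two of them, Wilcoxon signed-rank and Friedman, are within-subject tests without a group term. They can show that scores moved within an arm but not that arms differ. Among the rank tests named, only Mann-Whitney compares arms, and the text does not say whether it would be run on follow-up values or on changes.

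PASS and the ERP indices are the main support for the GPS result, and the ERP indices carry the stated neurocognitive objective. With roughly 27 to 30 per arm and FDR correction on top, precision is scarce. A baseline value that has been collected and predicts the follow-up value is a nearly free source of it.

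**Working it through.** **Inputs from the protocol article.** Sample size section: three groups, f = 0.40, two-sided alpha 0.05, power 0.90, 27 per group before dropout, about 10% dropout, 30 per group. Secondary outcomes section: a PASS "test–retest coefficient of 0.78 after 2 weeks".

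**Inputs assumed.** The week-0 to week-4 PASS correlation (rho) in this trial is not given, so 0.78 serves as a high value and 0.5 as a lower one. No ERP correlation is given; 0.3 to 0.7 is assumed. The pairwise difference of 0.5 SD is assumed. Variances at baseline and follow-up are taken as equal.

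**Step 1: the plan's own figure.** One-way ANOVA, noncentral F with lambda = N f² = 81 × 0.16 = 12.96 on 2 and 78 df: power 0.895. So 27 per group reproduces the stated 0.90 to within rounding, and 27 / (1 − 0.10) = 30.

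**Step 2: variance of the between-arm contrast**, in units of the variance from comparing follow-up values only:

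- follow-up values only: 1
- change score (the baseline-to-week-4 group-by-time contrast): 2(1 − rho)
- ANCOVA on own baseline: 1 − rho²

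The ratio of change score to ANCOVA is 2(1 − rho)/(1 − rho²) = 2/(1 + rho). The ratio of follow-up only to ANCOVA is 1/(1 − rho²).

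| rho | ANCOVA | change score | change / ANCOVA | follow-up only / ANCOVA |
|---|---|---|---|---|
| 0.3 | 0.91 | 1.40 | 1.54 | 1.10 |
| 0.5 | 0.75 | 1.00 | 1.33 | 1.33 |
| 0.7 | 0.51 | 0.60 | 1.18 | 1.96 |
| 0.78 | 0.39 | 0.44 | 1.12 | 2.55 |

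For PASS, a change-type analysis thus costs about 12% extra variance at rho 0.78 and 33% at rho 0.5. A lower rho makes the change score worse relative to ANCOVA, while it shrinks the gain over a follow-up-only comparison.

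**Step 3: pairwise power**, two-sided 0.05, 27 per arm, difference 0.5 SD, noncentral t with noncentrality 0.5 / sqrt(v × 2/27), where v is the variance factor from step 2. ANCOVA loses one degree of freedom; Mann-Whitney is given efficiency 0.955.

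| Analysis | rho 0.5 | rho 0.78 |
|---|---|---|
| Mann-Whitney on week-4 values | 42% | 42% |
| Change score | 44% | 78% |
| ANCOVA on own baseline | 55% | 82% |

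**Step 4: chance imbalance.** The between-arm baseline difference has standard error sqrt(2/27) = 0.27 SD. At rho 0.78 about 0.78 × 0.27 = 0.21 SD of it would carry into a follow-up-only contrast. That variation is already inside the unadjusted standard error of step 2, so it is the same loss in another form and is not added to it.

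**The case against.** The strongest reply is that the text fixes none of the inefficient analyses. The rank tests are options, repeated-measures ANOVA is supplementary, and the firm verb attached to Friedman governs only the fallback to that supplement. The mixed model is called the primary analytic strategy and is nowhere barred for PASS or ERP. A reader might infer that the plan commits secondary outcomes to unadjusted tests; it only permits them. This part of the reply stands.

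A reader might also infer that reusing the primary model for PASS would adjust for the wrong baseline, since it lists GPS and not PASS. The documents do not support that. Baseline is one of the model's time levels, so a PASS version would contain PASS at week 0, and its group-by-time contrast would compare changes from it. Repeated-measures ANOVA removes own-baseline differences in the same way. The fair comparison for these two is therefore the change-score line above, with its smaller loss.

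The large contrast of 42% against 55–82% holds only if Mann-Whitney is run on week-4 values alone, which the text does not state. The 0.78 is a 2-week figure from a previous study; selection on GPS of at least 70, a longer interval and treatment would probably lower it. Under randomisation, chance imbalance is not bias on average.

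Finally, detailed covariate lists are often left to a statistical analysis plan. But this section does name covariates for one model and tests for the rest. What it names for the rest omits own-baseline adjustment and includes tests that cannot compare arms.

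**Conclusion.** The point holds as a modest, nearly free gain in efficiency, not as a flaw in validity. As written, the section permits secondary and ERP comparisons that do not condition on the outcome's own baseline. For PASS the cost against own-baseline ANCOVA is about 12% more variance at rho 0.78 and 33% at rho 0.5 if a change-type analysis is used, or 4 and 11 points of pairwise power for an assumed 0.5 SD difference. It is larger (13 to 40 points) only if a rank test is applied to week-4 values alone. For the ERP indices the direction is the same, but the size rests wholly on assumed correlations: over rho 0.3 to 0.7, change scores have 1.54 to 1.18 times the ANCOVA variance, and follow-up-only comparisons 1.10 to 1.96 times. Separately, Friedman and signed-rank tests cannot supply the between-arm comparison, whatever the correlation.

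**What to change.** In the Data analysis section, state that between-arm comparisons of PASS and of each ERP index use a model of the post-baseline values on group (with visit and group-by-visit where there are several post-baseline visits), adjusted for that outcome's own baseline value, age and sex. For PASS this is baseline PASS; for an ERP index it is the matching baseline amplitude or latency from the same task condition. Keep Mann-Whitney and repeated-measures ANOVA as sensitivity checks, and describe Wilcoxon signed-rank and Friedman as within-arm descriptions only. If normality is doubtful, a rank-based ANCOVA or bootstrap intervals for the adjusted difference keep the baseline in use.

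The cost is two or three sentences, one degree of freedom per outcome, and a simple rule for participants who lack that baseline value, such as mean imputation of the covariate. No new data, visits or participants are needed.
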